### Assessment of treatment efficacy

#### Participant characteristics

Demographics assessment will include participant self-reported age, sex, gender, race, ethnicity, sexual orientation, socioeconomic status, employment status, disability status, educational attainment, relationship status, and religious affiliation. Chart and records review, including review of Veterans’ VA medical charts and official criminal history records, will be used to assess history of suicide-related behaviors and history of criminal-legal involvement.

The Level of Service / Case Management Inventory (LS/CMI; [31] will be used to assess risk of future criminal behavior. The LS/CMI is a semi-structured interview assessment based on the RNR model of criminal behavior. It has been widely validated, with the total score as a good predictor of later criminal behavior [49]. Scores are interpreted through comparison against normative data of over 150,000 North American offenders [31].

The Columbia Suicide Severity Rating Scale (C-SSRS; [50]) will be used to assess history of suicide-related behaviors, including suicidal thoughts and behaviors. The C-SSRS is a semi-structured interview that assesses prevalence, recency, and nature of prior suicide-related behaviors. It has been widely used in both VA- and civilian-based settings and demonstrates strong inter-rater reliability and validity in Veteran samples [51, 52].

Mental health diagnosis will be assessed using the Quick Structured Clinical Interview for DSM-5 (QuickSCID-5; [53], and the Structured Interview for DSM-IV Personality (SIDP-IV; [54]. Each is a semi-structured interview to assess for mental health conditions according to established diagnostic criteria.

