#### Secondary efficacy outcomes

To measure secondary outcomes, participants will complete a range of self-report measures, including the Beck Scale for Suicidal Ideation (BSS; [33], Screen for Nonsuicidal Self-Injury (SNSI; [56], The Measure of Criminogenic Thinking Styles (MOCTS; [57], Triarchic Psychopathy Measure (TriPM; [58]), Patient Health Questionnaire-9 (PHQ-9; [59], PTSD Checklist for DSM-5 (PCL-5; [60], Difficulties in Emotion Regulation-18 (DERS-18; [61], Alcohol Use Disorders Identification Test (AUDIT; [62]), Drug Abuse Screening Test (DAST-10; [63], DBT-J Case Management Checklist [64], Quality of Life Enjoyment and Satisfaction Questionnaire—Short Form (Q-LES-Q-SF; [65]), and Connor-Davidson Resilience Scale (CD-RISC; [66]). To complement these assessments, a chart and records review will be completed by an independent rater to assess for nature and total duration of VA-based mental health care received, presence and frequency of suicide-related behavior documented in VA electronic medical records, and presence and frequency of criminal recidivism (defined as new arrest, violation, order of protection, or incarceration) occurring during the study period.

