#### Assessment protocol

Each of the six assessment timepoints will include a combination of semi-structured interviews completed via video call (including LS/CMI at all timepoints, C-SSRS at baseline and final follow-up, and QuickSCID and SID-P-IV at baseline) and self-report questionnaires self-administered via Qualtrics. See Table 4. To minimize bias in assessment, all interviews will be completed by evaluators who are blind to participant condition. Veterans will receive monetary compensation ($75) for each completed assessment; a completion bonus ($75) will also be provided at the end of study participation to participants who complete all assessment timepoints to encourage retention throughout the follow-up period. A random 20% of interviews will be recorded and reviewed by a second rater to assess fidelity to assessment administration protocols and determine inter-rater reliability.

**Table 4 Tab4:** Projected assessment schedule

Assessment	Construct	Baseline	8 weeks	16 weeks	28 weeks	40 weeks	52 weeks
Participant Characteristics							
Demographic Assessment	Demographic background	X					X
Chart & Records Review	Psychiatric treatment history, Military service history, Suicide-related behavior history, History of criminal-legal involvement						X*
QuickSCID / SID-P-IV	Mental health diagnoses	X					
C-SSRS	Suicide-related behavior history	X					X*
Primary Outcomes							
LS/CMI	Risk for criminal behavior, History of criminal-legal involvement	X	X	X	X	X	X
IPF	Psychosocial functioning	X	X	X	X	X	X
Secondary Outcomes							
BSS	Risk for suicide-related behavior	X	X	X	X	X	X
SNSI	Non-suicidal self-injury	X		X			X
DERS-18	Emotion regulation difficulties	X	X	X	X	X	X
TriPM	Psychopathic personality traits	X		X			X
MOCTS	Criminogenic thinking style	X		X			X
PHQ-9	Psychological distress	X	X	X	X	X	X
AUDIT	Alcohol use	X	X	X	X	X	X
DAST-10	Non-alcohol substance use	X	X	X	X	X	X
DBT-J CM Checklist	Case management needs	X	X	X	X	X	X
Q-LES-Q-SF	Quality of life	X	X	X	X	X	X
CD-RISC	Resilience	X	X	X	X	X	X
PCL-5	PTSD symptom severity	X		X			X

^*^Or at time of study termination

A data safety monitoring board (DSMB) comprised of research psychologists with experience in high-risk Veteran populations and intervention development research will aid in monitoring ongoing data collection to evaluate for potentially adverse effects of study participation. Collected data will be shared with the DSMB at least quarterly or within 48 h of an adverse event, whichever occurs first.

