### Data analysis plan

Analyses will employ an alpha of 0.05, use two-tailed tests, and be completed using SPSS and/or the R Computing Environment. Preliminary analyses will include computing descriptive statistics and inspecting data to determine whether data transformations are needed, statistical assumptions are met, and psychometric properties of each scale are sound. Multiple imputation will be used for transient missing data. Because participants who dropout of the protocol may be qualitatively distinct from protocol completers (e.g., due to differences in motivation, legal requirements, etc.), analyses will also include a sensitivity analysis by comparing the full “intent-to-treat” sample against protocol completers. Potential confounders, including duration of outside treatment services received during the intervention period, will be compared across conditions and included as covariates in subsequent analyses if significantly related to study outcomes.

Primary and secondary analyses will be investigated using analyses of covariance to compare participants in the DBT-J and supportive group conditions on primary and secondary continuous treatment targets at post-treatment after controlling for baseline scores. Poisson regression with robust error variance will similarly be used to compare DBT-J and comparison conditions on dichotomous secondary treatment targets (suicide attempt during study period and criminal recidivism during study period). The DBT-J condition will be considered superior to the supportive group condition if participants in the DBT-J condition demonstrate statistically superior scores on either primary treatment target at post-treatment. The DBT-J intervention will be considered efficacious if results suggest (a) superiority to the supportive group condition and (b) clinically significant change in primary efficacy outcomes from baseline to post-treatment among DBT-J participants [67].

To support exploratory analyses comparing efficacy of DBT-J programming across VCLI subgroups, DBT-J participants will be coded according to most recent offense type (violent or nonviolent), presence of a substance use disorder, and presence of a severe mental illness (i.e., mood or psychotic disorder). Multivariate analyses of covariance will be used with subgroup membership included as predictor variables, LS/CMI and IPF post-treatment scores included as dependent variables, and LS/CMI and IPF baseline scores included as covariates.

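### Baseline LS/CMI is not fixed in advance as a covariate in the criminal recidivism model; as written, it can enter only through a significance screen

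*Protocol article*

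**What the plan says.** The Data analysis plan compares the arms on "continuous treatment targets at post-treatment after controlling for baseline scores". The next sentence turns to the binary outcomes: "Poisson regression with robust error variance will similarly be used to compare DBT-J and comparison conditions on dichotomous secondary treatment targets", namely "suicide attempt during study period and criminal recidivism during study period". No covariate is named for this second model.

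A general covariate rule stands earlier in the same section. Potential confounders "will be compared across conditions and included as covariates in subsequent analyses if significantly related to study outcomes". The one example given is the duration of outside treatment during the intervention period. Baseline LS/CMI is not mentioned there.

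Under Secondary efficacy outcomes, the records review captures "criminal recidivism (defined as new arrest, violation, order of protection, or incarceration) occurring during the study period". Under Participant characteristics, the LS/CMI is described as widely validated, "with the total score as a good predictor of later criminal behavior". The Assessment protocol lists the interviews, "including LS/CMI at all timepoints", and Table 4 marks it at baseline with the construct label "Risk for criminal behavior, History of criminal-legal involvement".

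**The concern.** Each continuous outcome has a baseline value of its own, and the plan commits to adjusting for it. Recidivism during the study has no such value, so the same principle cannot be carried over without naming a substitute. The article identifies a natural substitute and collects it, but does not assign it to the outcome that it is said to predict.

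That leaves the significance rule. Under it, whether the model is adjusted depends on the outcome data, and it is not even clear that baseline LS/CMI is among the variables to be screened.

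Two things are at stake. One is precision, on a yes/no outcome in about 200 people that the sample size was not built around. The other is chance imbalance: randomization is stratified by region only, so baseline criminogenic risk is balanced only in expectation.

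**Working it through.** **The plan's own figure.** Justification of sample size gives 80 per arm for 80% power at d = 0.50 and α = 0.025, and 100 per arm after 20% dropout. A two-sided t test needs 78 per arm (80.4% power; 81.5% at 80 per arm), and 80 / (1 − 0.20) = 100. The figure reproduces, but it concerns the continuous primary outcomes. No rate, effect or power is stated for recidivism.

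**Inputs for recidivism.**
- From the article: 100 per arm, two-sided α = 0.05, robust Poisson regression.
- Assumed, because the article gives none: comparator risk p0, rate ratio RR, and AUC of baseline LS/CMI for recidivism. The AUC is turned into a standardized separation by δ = √2 × Φ⁻¹(AUC): 0.545, 0.742 and 0.954 for AUC 0.65, 0.70 and 0.75.

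**Crude standard error.** SE(log RR) = √[(1 − p1)/(n·p1) + (1 − p0)/(n·p0)]. With p0 = 0.30, RR = 0.60 and n = 100 per arm, p1 = 0.18 and SE = √(0.82/18 + 0.70/30) = √0.0689 = 0.262. The simulated crude mean is 0.267-0.268. The usual two-proportion formula gives 51.1% power, against 50.2-51.1% simulated, so the simulation is sound.

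**With and without baseline LS/CMI** (RR 0.60, 3,000 simulated trials per row; variance reduction = 1 − (adjusted SE / crude SE)²):

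| p0 | AUC | SE crude | SE adjusted | Variance reduction | Power crude | Power adjusted |
|---|---|---|---|---|---|---|
| 0.20 | 0.65 | 0.348 | 0.343 | 2.9% | 32.0% | 33.1% |
| 0.20 | 0.70 | 0.349 | 0.340 | 5.1% | 32.1% | 33.4% |
| 0.20 | 0.75 | 0.347 | 0.333 | 7.9% | 31.0% | 34.0% |
| 0.30 | 0.65 | 0.267 | 0.262 | 3.7% | 50.9% | 52.6% |
| 0.30 | 0.70 | 0.268 | 0.259 | 6.6% | 50.2% | 52.5% |
| 0.30 | 0.75 | 0.268 | 0.255 | 9.5% | 51.1% | 55.6% |
| 0.50 | 0.65 | 0.184 | 0.181 | 3.2% | 82.8% | 83.6% |
| 0.50 | 0.70 | 0.185 | 0.179 | 6.4% | 84.0% | 85.3% |
| 0.50 | 0.75 | 0.185 | 0.176 | 9.5% | 84.3% | 86.4% |

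For the middle row (p0 = 0.30, AUC 0.70), the interval on the log scale is 1 − 0.259/0.268 = 3.4% narrower. That equals about 1/0.934 − 1 = 7% more participants, or some 14 of 200.

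**Other assumed effects.** At RR 0.65-0.70 and p0 of 30-50%, the variance falls by about 3-11%. Examples of power are 54.4% to 57.8% (p0 = 0.50, RR 0.70, AUC 0.70) and 40.9% to 46.4% (p0 = 0.40, RR 0.70, AUC 0.75). At RR 0.67 over p0 of 20-50%, the variance falls by about 3-15% and power rises by about 1-6 points.

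**No effect (RR 1.0, p0 = 0.30).** Rejection is 4.1-4.7% crude and 4.3-5.2% adjusted.

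**Chance imbalance.** With 100 per arm, the arm difference in mean baseline LS/CMI has a standard error of √(1/100 + 1/100) = 0.141 SD. Differences up to 1.96 × 0.141 = 0.28 SD in either direction are ordinary. A crude comparison leaves them in the estimate.

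**The case against.** **The article never says that the model is unadjusted.** A reader might infer from the missing covariate that the plan has chosen a crude comparison of two proportions. The text does not support that. The sentence follows one on baseline adjustment and is linked to it by the word similarly, and an article may leave the covariates of a secondary model to a fuller plan. This stands, and for that reason silence alone is not the point. The point is the rule that is written down: it makes entry depend on outcome data and does not name baseline LS/CMI.

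**The screen may admit it anyway.** A reader might take the rule as a test of differences between the arms. Arms are compared, but the condition for entry is association with the outcome, which is a prognostic criterion. If baseline LS/CMI were screened at 0.05 in 200 participants (assumed comparator risk 30-50%, RR 0.65), it would pass in about 89-95% of trials at AUC 0.65, about 99% at 0.70 and nearly all at 0.75. This stands too: if it is screened, most of the loss disappears. But nothing says that it will be screened, and a covariate wanted in nearly every case is better named in advance.

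**Neither validity nor the trial's main conclusion is affected.** Randomization makes the unadjusted ratio valid, and superiority and efficacy are judged on the primary targets. This stands in full.

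**The size is uncertain.** The article calls the LS/CMI a good predictor in general, not in Veterans or for an outcome that also counts violations and orders of protection. This stands, and is why only a range is given.

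**Conclusion.** The point holds as a free improvement. The Data analysis plan does not fix baseline LS/CMI in the recidivism model, although the article endorses it as a predictor and schedules it at baseline.

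The expected gain is modest: roughly 3-15% less variance of the log rate ratio and about 1-6 points of power, plus correction for chance imbalance. This rests on an assumed comparator risk of 20-50%, a rate ratio near 0.65-0.70, an AUC of 0.65-0.75 and all 200 participants contributing. A weaker predictor gives less: at AUC 0.60 and RR 0.60 the gain is negligible.

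It would go too far to say that the plan discards a large amount of information or that its recidivism result would be biased. The figures show a small gain, and type I error is near nominal either way.

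**What to change.** In the Data analysis plan, state that the recidivism model contains condition and baseline LS/CMI total as a continuous covariate for every participant, fixed in advance and not subject to the significance screen. Report the adjusted rate ratio as the main result, with the unadjusted ratio alongside.

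The cost is one sentence. No new data are needed and the sample size does not change. The sentence should be in place before anyone sees recidivism by arm.

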### Study aims

Study design was guided by the following aims:*Primary Aims*: Assess the superiority of DBT-J over supportive group therapy in (a) decreasing risk of future criminogenic behavior and (b) increasing psychosocial functioning.*Secondary Aim*: Assess the superiority of DBT-J over supportive group therapy in improving secondary treatment targets (i.e., suicide-related thoughts and behaviors, criminogenic thinking, psychopathic personality traits, psychological distress, emotion dysregulation, posttraumatic stress, substance use, case management needs, quality of life, resilience, and criminal recidivism).*Exploratory Aim 1*: Assess for differential efficacy of DBT-J across VCLI subgroups (i.e., violent versus nonviolent most recent offense type, presence/absence of a substance use disorder, and presence/absence of a severe mental illness).*Exploratory Aim 2*: Assess long-term impact of DBT-J participation (versus participation in supportive group therapy) on primary efficacy outcomes.

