Lastly, exploratory analyses will examine potential long-term consequences of participation in DBT-J versus supportive group therapy on primary efficacy outcomes. Two repeated-measures analyses of variance will be used with condition included as the independent variable and LS/CMI or IPF total scores at each assessment timepoint included as dependent variables.

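### Exploratory Aim 1 asks about differential efficacy, but its analysis uses only the DBT-J arm and cannot separate effect modification from prognosis

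*Protocol article*

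**What the plan says.** The Study aims section words Exploratory Aim 1 as "Assess for differential efficacy of DBT-J across VCLI subgroups". The factors are violent or nonviolent most recent offence, substance use disorder, and severe mental illness. The Data analysis plan repeats the purpose: "To support exploratory analyses comparing efficacy of DBT-J programming across VCLI subgroups".

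The same sentence then names who is coded: "DBT-J participants will be coded according to most recent offense type (violent or nonviolent), presence of a substance use disorder". The model follows: "Multivariate analyses of covariance will be used with subgroup membership included as predictor variables", with post-treatment LS/CMI and IPF as the dependent variables and "LS/CMI and IPF baseline scores included as covariates". The supportive group does not appear, nor does a condition term or an interaction.

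Two other statements in the Data analysis plan bear on this:

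- The trial's own definition of efficacy requires the comparator: "The DBT-J intervention will be considered efficacious if results suggest (a) superiority to the supportive group condition", together with clinically significant change among DBT-J participants.
- For Exploratory Aim 2 the comparator is in the model: "Two repeated-measures analyses of variance will be used with condition included as the independent variable".

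**The concern.** Differential efficacy means that the difference between DBT-J and supportive therapy varies by subgroup. An analysis of one arm does not estimate that difference in any subgroup. It estimates how post-treatment scores differ between subgroups of people who all received DBT-J.

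Offence type, substance use disorder and severe mental illness could each plausibly relate to outcome under either treatment. Adjusting for baseline score does not remove differences in natural course, in outside care (which both arms may continue) or in regression to the mean. The article's section on the need for continued research makes the same criticism of the earlier pre-post studies: without a control condition, effects of time and outside services cannot be excluded.

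At stake is a subgroup statement. The trial could report that DBT-J works less well in Veterans with, say, substance use disorder when the treatment effect is the same. It could also miss a real difference. The article notes that such difficulties are common exclusion criteria elsewhere, so a wrong subgroup statement could carry weight.

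**Working it through.** **1. The plan's own figure.** The article gives no figure for Exploratory Aim 1. Its sample size for the primary aims (d = 0.50, two-sided alpha 0.025, 80% power) reproduces: a t-test needs 77.3, so 78 per arm, against the stated 80; power at 80 per arm is 0.815; and 80/(1 − 0.20) = 100 per arm. The sample size is not in dispute. It supplies the 80 DBT-J participants expected at post-treatment.

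**2. What each contrast estimates.** Write the expected post-treatment score, given baseline, as a + d·T + g·S + h·T·S. Here T is 1 for DBT-J, S is subgroup membership, g is the prognostic difference and h is the effect modification.

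- Planned contrast (T = 1 only): (a + d + g + h) − (a + d) = g + h.
- Aim as worded: h.

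The planned contrast equals the target only if g = 0, and data from the DBT-J arm alone cannot check that. More participants do not help.

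**3. False signals, h = 0.** The documents give no subgroup shares or prognostic gaps for this trial, so these are assumed. The test is a two-sample t-test on one outcome, with two-sided alpha 0.05 from the plan ("Analyses will employ an alpha of 0.05, use two-tailed tests"). SE = sqrt(1/n1 + 1/n2) in SD units, which is 0.224 at 40/40.

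| Prognostic gap (SD) | 40/40 | 53/27 | 64/16 |
|---|---|---|---|
| 0.2 | 14% | 13% | 11% |
| 0.3 | 26% | 24% | 19% |
| 0.4 | 42% | 39% | 29% |
| 0.5 | 60% | 55% | 42% |

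The 53/27 column matters for substance use disorder, because the article reports about two-thirds in the pilots and 69% in the wider population. A valid interaction test rejects 5% of the time in every cell.

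The rates are higher if the gap is what remains after adjusting for a correlated baseline. In a simulation of one outcome (3,000 runs, 80 per arm, 50/50 split, baseline coefficient 0.6, residual SD 0.8), the DBT-J-only test rejected in 37% of trials at 0.3 SD and 78% at 0.5 SD. The two-arm interaction test stayed at 4–5%.

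**4. Masking.** In the same simulation with h = 0.5 SD and g = −0.5 SD, g + h = 0. The DBT-J-only test rejected in 4.9% of trials and the interaction test in 48%.

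**5. Precision of the interaction test.** With 80 per arm and the same split in both arms, the interaction SE is sqrt(2) times the within-arm SE. The detectable interaction at 80% power is (1.96 + 0.84) × SE. The power column is for an interaction of 0.5 SD.

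| Split | Interaction SE | Detectable (SD) | Power |
|---|---|---|---|
| 50/50 | 0.316 | 0.89 | 35% |
| Two-thirds/one-third | 0.334 | 0.94 | 32% |
| 80/20 | 0.395 | 1.11 | 24% |

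These ignore any gain from baseline adjustment. With the assumed baseline coefficient of 0.6, simulated power at 50/50 is about 49%.

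**The case against.** The strongest reply is that this is a labelled exploratory aim. It feeds neither the superiority rule, nor the efficacy rule, nor the sample size. The article also speaks elsewhere of differences in treatment response, which one arm can describe. And the valid interaction test has low power, so the trial may learn little from it.

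The first part stands and limits the severity. The second shows that a legitimate one-arm question exists, but it is not the one written in the Study aims or repeated in the analysis plan. The third argues for reporting estimates with intervals. It does not justify a contrast that estimates another quantity.

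Nor is this a detail left to a fuller plan: the article itself states the population and the model terms.

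A reader might also infer more than the documents support:

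- That the planned analysis measures prognosis alone. It measures prognosis plus effect modification, inseparably.
- That 60% is the false-positive rate of the planned test. It comes from an unadjusted t-test on one outcome under assumed inputs; the plan specifies a two-outcome MANCOVA with baseline covariates.
- That the article calls the exclusion of these subgroups elsewhere wrong. It says only that such exclusion is common.
- That every subgroup variable is already a baseline measure. Diagnoses are, in Table 4. The source for most recent offence type is not stated, and Table 4 schedules the chart and records review at week 52 or study termination.

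**Conclusion.** The point holds. As written, the analysis of Exploratory Aim 1 cannot answer its stated question at any sample size, because it leaves out the arm that the article's own definition of efficacy requires. The algebra in step 2 needs no numerical assumption.

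The size of the resulting error does rest on assumptions. For prognostic gaps of 0.2 to 0.5 SD and splits from 50/50 to 80/20, the illustrative false-signal rate runs from about 11% to 60%, and higher if the gap persists after adjustment for a correlated baseline. If no factor is prognostic, the planned contrast has no such bias.

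Severity is moderate. It would be tempting to treat this as a threat to the trial's main result, but the primary and secondary comparisons use both arms and are untouched.

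**What to change.** Either of two changes resolves the mismatch.

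**Keep the aim and change the analysis.** Code the three factors in both arms from information dated at or before randomisation: the baseline QuickSCID for diagnoses, and the baseline LS/CMI history, or records restricted to pre-randomisation offences, for offence type. Add condition and condition by subgroup to the existing model. The MANCOVA can stay; an ANCOVA per outcome would also serve. Report the interaction estimates with confidence intervals and the between-arm differences within each subgroup, labelled exploratory. State the low precision shown in step 5, so that a non-significant interaction is not read as equal efficacy.

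**Keep the analysis and change the aim.** Reword it as predictors of post-treatment outcome among DBT-J participants, and draw no conclusion about differential efficacy.

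The first option needs no new assessments, since diagnoses and criminal-legal history are planned for all participants. It costs revised analysis wording, coding of the second arm and a stated source and cut-off date for offence type. The second costs wording only, but gives up the question.

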## Randomized clinical trial

A multisite randomized Stage III clinical trial will be conducted to assess the efficacy of DBT-J. A total of 200 Veterans will be recruited across three regions in the U.S. (VA VISNs 2, 19, and 21) over three years (2024–2026; anticipated date of recruitment completion, June 30, 2026). Random assignment, stratified by region and generated using an electronic random number generator, will be used to assign participating Veterans to DBT-J or a supportive group therapy condition. Assignment will be completed immediately after enrollment and available only to the PI and individuals involved in intervention delivery; assignment is masked from individuals involved in assessment completion. Veterans will receive 16 weeks of assigned intervention followed by a 36-week observation period. To inform evaluations of treatment efficacy, participants will also complete assessments in 8-week intervals during the intervention period beginning at baseline and 12-week intervals during the follow-up period (6 times total). See Table 2. All protocols were developed in accordance with the Declaration of Helsinki and have been approved by the VA Central Institutional Review Board; protocols and analysis plans are pre-registered through clinicaltrials.gov (NCT05974553, registered July 26, 2023). All participants will provide informed consent prior to participation. To preserve participant confidentiality, individual participant data will not be shared with anyone outside of the immediate research team.

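### The repeated-measures ANOVA stated for Exploratory Aim 2 (long-term impact) has no term that tests the arm difference during follow-up, weeks 28 to 52

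*Protocol article*

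**What the plan says.** Under Study aims, Exploratory Aim 2 is to "Assess long-term impact of DBT-J participation (versus participation in supportive group therapy) on primary efficacy outcomes". The last paragraph of the Data analysis plan repeats the purpose and names one method: two repeated-measures ANOVAs, one per primary outcome, "with condition included as the independent variable and LS/CMI or IPF total scores at each assessment timepoint included as dependent variables".

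The section Randomized clinical trial sets the assessments at "8-week intervals during the intervention period beginning at baseline and 12-week intervals during the follow-up period (6 times total"). Table 4 gives them as baseline and weeks 8, 16, 28, 40 and 52. Treatment lasts 16 weeks, so three of the six visits fall before, during or at the end of treatment.

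The primary analysis treats baseline differently. It is an ANCOVA comparing the arms "on primary and secondary continuous treatment targets at post-treatment after controlling for baseline scores".

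The plan does not say which ANOVA term answers Aim 2, and it names no contrast within follow-up.

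**The concern.** A two-arm, six-visit repeated-measures ANOVA gives two tests that involve condition, and neither is about follow-up.

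- **Condition main effect.** This is the arm difference averaged over all six visits. One is a randomised baseline, where the expected difference is zero, and two are the week 8 and week 16 visits.
- **Condition by time.** This is a 5-df omnibus test. It responds to any change in the arm difference across visits, including one confined to weeks 8 and 16.

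Either test can be significant because of the week-16 effect that the primary ANCOVA already examines. A real lasting effect, on the other hand, is diluted in the main effect by the baseline visit. What is at stake is whether the three follow-up visits answer the question they were scheduled for. The problem does not depend on missing data; it is there when every visit is complete.

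**Working it through.** **Inputs from the protocol.** Visits at weeks 0, 8, 16, 28, 40 and 52; treatment for 16 weeks; two-sided alpha 0.05; planning effect d = 0.50; 80 analysable per condition.

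**Assumptions not in the protocol.** SD 1 at every visit; complete data; between-visit correlation ρ equal at all lags (0.5 to 0.7), or decaying as 0.8 per 12 weeks; the effect patterns named below.

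**The plan's own figure.** No power or decision rule is given for Aim 2. The primary-aim sample size holds up: an exact two-sided t calculation at d = 0.50 and alpha 0.025 needs 78 per arm for 80% power and gives 81.5% at 80. With 20% dropout, 80/0.8 = 100 per arm. I use 80 per arm below.

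**1. Main effect when the benefit ends at week 16.** Arm differences are (0, 0.50, 0.50, 0, 0, 0).
- Average difference: 1.00/6 = 0.167.
- Variance of a participant's six-visit mean: (1 + 5ρ)/6 = 0.583 at ρ = 0.5 and 0.750 at ρ = 0.7.
- Noncentrality: 0.167/√variance × √(80/2) = 1.38 and 1.22.
- Probability of significance (158 df): 27.9% and 22.7%. With decaying correlation the variance is 0.711, the noncentrality 1.25 and the probability 23.7%.

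Simulations of the same scenario scattered around these values, at 21–30%.

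**2. Condition by time, effect ended versus effect sustained.** With equal correlation, λ = (n/2) × Σ(δ − mean δ)²/(1 − ρ), on 5 and 790 df.
- Ends at week 16: Σ = 0.50 − 6 × 0.167² = 0.333. λ = 40 × 0.333/0.5 = 26.7 at ρ = 0.5 and 44.4 at ρ = 0.7. Power is 98.9% and over 99.9%.
- Sustained d = 0.50 at all five post-baseline visits: Σ = 1.25 − 6 × 0.417² = 0.208. λ = 16.7 and 27.8. Power is 90.2% and 99.2%.

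Σ is larger for the effect that vanished than for the one that lasted, so a significant interaction does not favour durability. Simulation with Greenhouse-Geisser correction agrees: 99–100% (96–100% if 65 per arm is included) against 90–99%.

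**3. Follow-up contrast, same ended-at-16 scenario.** The expected difference over weeks 28–52 is zero, so a baseline-adjusted contrast rejects at its nominal 5%. Simulated rates were 4.2–5.7%, for the weeks 28–52 average and for week 52.

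**4. Power with a sustained d = 0.35.** The main effect sees 0.35 × 5/6 = 0.292, with the variance in step 1. The weeks 28–52 average has residual variance (1 + 2ρ)/3 − ρ² after baseline adjustment (0.417 at ρ = 0.5, 0.310 at ρ = 0.7). Week 52 alone has 1 − ρ² (0.75, 0.51).

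| Test | ρ = 0.5 | ρ = 0.7 | Decaying |
|---|---|---|---|
| Main effect, all six visits | 67.0% | 56.2% | 58.5% |
| Adjusted average, weeks 28–52 | 92.6% | 97.7% | 81.2% |
| Adjusted difference, week 52 | 71.9% | 86.9% | 66.2% |

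With simulation included, the ranges are 56–69%, 80–98% and 65–87%.

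**5. Smaller early effect.** With 0.15 at week 8, 0.30 at week 16 and zero after, the interaction is significant in 44–71% of trials and the main effect in roughly 8–9.5%.

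**The case against.** A reader might infer that the trial will report a lapsed effect as lasting benefit. The documents do not support that. The plan attaches no decision rule to the ANOVA and nowhere says that a significant interaction will be read as durability. In the ended-at-16 scenario the arm difference really does change over time, so a 99–100% interaction rate is correct detection of that change. It is not a false-positive rate for a long-term claim. The scenario is also severe: full effect by week 8 and exactly zero by week 28. Step 5 shows how far the rates fall when the early effect is smaller.

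Three further points are fair. Long-term course can be viewed as a trajectory, for which earlier visits are useful reference points. Baseline in the outcome vector is a valid parameterisation under randomisation. And visit-specific comparisons may be set out in an analysis plan that is not shown.

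These points limit the concern without removing it. A trajectory analysis still needs a stated contrast to say whether the arms differ in follow-up. The objection is to the model the article does state, whose outcome vector and terms do not match its own aim, so an unseen plan would have to redirect that analysis as well as add detail. The gain from changing it also depends on the contrast chosen: it is large for the follow-up average and more modest for week 52 alone.

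**Conclusion.** The point holds as a mismatch between aim and analysis. As stated, the ANOVA cannot by itself say whether DBT-J differs from supportive group therapy during weeks 28–52. If d = 0.50 were present only at weeks 8 and 16, the main effect would be significant about four to six times as often as a test of follow-up should be. The interaction would be significant in most trials whether the benefit lasted or not. If a benefit of d = 0.35 were sustained, the main effect would give up roughly 25 to 40 percentage points of power against the adjusted follow-up average, and about 5 to 31 against week 52.

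The sizes rest on the assumed SDs, correlations, effect patterns and complete data. The mismatch itself does not. The consequence is confined to an exploratory aim: superiority and efficacy are judged at post-treatment, and neither that rule nor the sample size depends on this analysis.

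**What to change.** In the last paragraph of the Data analysis plan:

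1. Take baseline out of the outcome vector and enter it as a covariate, as the primary ANCOVA does.
2. Model the post-baseline scores with condition, visit and condition-by-visit terms.
3. Prespecify one baseline-adjusted between-arm follow-up contrast, with its 95% CI, as the Aim 2 result for each outcome. The weeks 28–52 average has more power; week 52 describes the end of observation. Either is defensible if chosen in advance.
4. Report the visit-specific adjusted differences alongside it.
5. State that neither an all-visit main effect nor the omnibus interaction alone will be taken as evidence of long-term impact.

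The cost is wording only: same visits, same data and same sample size. It should be settled before any unblinded analysis.
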